Rybniker et al1 recently used an intracellular assay procedure to screen for drugs with antituberculous potential. They found that lansoprazole was highly active against TB in cell culture, when transformed intracellularly from the prodrug lansoprazole to lansoprazole sufoxide. Strong activity was also found against drug-resistant TB clinical isolates suggesting further clinical investigation is warranted. Of note, other PPIs (omeprazole and pantoprazole) were not found to have anti-tuberculous activity. To date there have been no clinical studies assessing whether lansoprazole as used in routine clinical care has such anti-tuberculous properties. Given the widespread use of PPIs over many years, we believe the CPRD provides an ideal opportunity to investigate whether lansoprazole may be associated with a lower risk of TB disease by making a direct comparison between lansoprazole users and users of omeprazole or pantoprazole.

1. **Study Type**

This is a hypothesis testing study

1. **Study Design**

This will be a cohort study comparing the rate of TB disease in people treated with lansoprazole, compared with people treated with omeprazole or pantoprazole. This design will minimise confounding because both lansoprazole exposed and unexposed patients will be receiving a PPI and will therefore have similar underlying health problems which may be associated with the risk of TB disease.

1. **Sample Size**

A feasibility count from Jan 2015 CPRD GOLD indicates the following:

- Lansoprazole new users n=744,144
- Omeprazole and pantoprazole new users n=1,182,888
- Lansoprazole new users with subsequent TB n=1,227

At this stage we cannot be sure how many incident TB cases will occur during PPI exposure, rather than after exposure has ended. Nor can we state with confidence what effect size we expect to detect. Table 1 therefore gives estimates of power under a range of assumptions, based on a conservative 1:1 comparison between lansoprazole and omeprazole or pantoprazole.

|  | *Number of exposed cases* | | | |
| --- | --- | --- | --- | --- |
| *Relative Risk* | **1,200** | **800** | **500** | **200** |
| **0.9** | 0.73 | 0.56 | 0.38 | 0.18 |
| **0.8** | >0.99 | >0.99 | 0.94 | 0.61 |
| **0.7** | >0.99 | >0.99 | >0.99 | >0.99 |
| **0.6** | >0.99 | >0.99 | >0.99 | >0.99 |
| **0.5** | >0.99 | >0.99 | >0.99 | >0.99 |

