Table 1: Estimates of power to detect a range of possible relative risks, under a range of assumptions about the number of likely lansoprazole exposed TB cases

For most of the assumptions tested, we will have adequate power to detect an association with lansoprazole assuming a protective association of 0.8 or greater, which we believe would represent a clinically relevant effect size.

1. **Data Linkage Required (if applicable)**

Patient-level index of multiple deprivation data are required to assess for confounding as it is likely that risk of TB will vary by socioeconomic status. Since this is only available for patients in the linkage scheme, we propose to use practice-level index of multiple deprivation for the remainder of patients (rescaled to be on the same scale as the patient level scores, using observations where both are available). We have used this strategy successfully in previous CPRD studies.

We will also use HES (in- and out-patient data) to identify cases of TB recorded in hospital.

1. **Study Population**

The source population for this study is all patients aged 16 years or over with acceptable user status registered in the entire CPRD, with up-to-standard (uts) follow up of at least 12 months.

From the source population we will select all patients who are:

1. New users of lansoprazole; defined as people starting treatment with lansoprazole after at least 12 months uts follow up, with no previous record of receiving a PPI.
2. New users of omeprazole or pantoprazole; defined as people starting treatment with omeprazole or pantoprazole after at least 12 months uts follow up, with no previous record of receiving a PPI.

Exposure to lansoprazole, omeprazole and pantoprazole will be defined by prescription records, as conducted previously by this research group2.

All patients with a record of TB disease prior to their first PPI will be excluded from the study.

1. **Selection of comparison group(s) or controls**

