End of follow up will be defined as the earliest of first recorded TB disease, death, transfer away, end of UTS or last data collection date.

Examples of how patient follow up time will be allocated are shown in Figure 1.

*Figure 1: Example Patient Exposure Timelines*

1. Lansoprazole exposure only

12 months follow up with no PPI

End uts

Lansoprazole prescription

EXPOSURE GROUP

Lanoprazole

1. Omeprazole or pantoprazole only

12 months follow up with no PPI

End uts

Omeprazole prescription

EXPOSURE GROUP

Omeprazole

or pantoprazole

1. Lansoprazole and omeprazole/pantoprazole

12 months follow up with no PPI

End uts

Lansoprazole prescription

Omeprazole prescription

EXPOSURE GROUP

Lansoprazole

Omeprazole

or pantoprazole

4. Lansoprazole with Breaks

12 months follow up with no PPI

End uts

Lansoprazole prescription

EXPOSURE GROUP

Lansoprazole

Unexposed

5. Lansoprazole, omeprazole/pantoprazole and breaks

12 months follow up with no lansoprazole

End uts

Pantoprazole prescription

Lansoprazole prescription

EXPOSURE GROUP

Lansoprazole

Unexposed

Omeprazole

or pantoprazole

The primary comparison of interest is the risk of TB comparing lansoprazole exposed time with omeprazole or pantoprazole exposed time. People starting treatment with omeprazole or pantoprazole but later receiving lansoprazole will transition to the lansoprazole group at that time and vice versa. Follow up for each patient will end at the earliest of; TB disease, transfer out, death or end of uts follow up.

Descriptive analyses will be performed, comparing the distribution of the following variables between patients starting lansoprazole and those starting omeprazole/pantoprazole: Age, sex, calendar year, smoking behaviour, body mass index, alcohol use, ethnicity, drug abuse, the use of corticosteroids, any record signifying any prior use of chemotherapy, travel vaccines, antimalarials, diabetes , rheumatoid arthritis, irritable bowel disease, chronic obstructive pulmonary disease, asthma, chronic kidney disease, depression, leukaemia, lymphoma, myeloma, a record of HIV infection and index of multiple deprivation score.

Cox regression will be used to estimate hazard ratios and 95% confidence intervals, comparing lansoprazole exposed time against omeprazole or pantoprazole exposed time. A crude model will be constructed with just the main exposure variable, followed by a model adjusting for potential confounders.

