We will fit an interaction term to look for effect modification between lansoprazole exposure and age.

As a sensitivity analysis we will vary the time following the end of estimated treatment duration after which therapy cessation is assumed, from 60 to 90 days. A further sensitivity analysis will censor all patients after a cessation or switch of PPI therapy, (cessation defined as longer than 60 days not covered by a prescription.)

1. **Plan for addressing confounding**

Potentially confounding variables have been selected based on their possible association with the risk of TB, as listed in part K. These variables will be explored and potentially adjusted for in a multivariable Cox regression model. However, we believe substantial confounding is unlikely in this study as risk factors for TB are not expected to be associated with the choice of specific PPI, with the exception of calendar year. It is possible that rates of TB have changed over time and local prescribing guidance for preferred PPI has varied over the years mainly based on cost considerations. PPI preference could also be dictated by differential drug interactions between individual PPIs, as noted above for tacrolimus and ciclosporin and people with a history of taking either drug will be excluded.

1. **Plan for addressing missing data**

There is known missingness in the smoking and alcohol status and BMI variables. From previous experience of studies involving people taking long term medication such as PPIs it is expected that <10% of patients will have missing data. We plan to conduct a complete case analysis, which relies on the assumption that the probability of these data being missing is independent of TB risk, conditional on covariates5; given the small amount of missing data, any violation of the assumption is unlikely to importantly affect the results. Ethnicity is likely to have substantially more missing data. Again, we will conduct a complete case analysis with this variable included in the model, recognising the reduction in sample size will be greater and that this is a limitation of the study.

1. **Limitations of the study design, data sources and analytical methods**

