It is possible that TB may go unidentified in some patients and therefore unrecorded in CPRD. Assuming this is non-differential between PPIs, this will only lead to a loss of power, rather than a biased estimate; however the power calculations we present are based on identified cases and so this is not expected to be a major limitation.

The timing of TB disease recorded in CPRD will not be the same as the date when infection actually occurred as we are detecting recorded diagnoses rather than actual time of infection. We are dealing with this by moving the date of TB disease to an earlier time and have planned sensitivity analyses varying the length of this time shift. However, PPI exposure tends to be for long periods in many patients and so it is not expected that timing inaccuracy for infection will have a substantial impact on the estimated exposure status of cases.

The recording of risk factors for TB is unlikely to be perfect. For example HIV status, drug abuse and exposure to chemotherapy may not be well recorded in primary care. However, we anticipate little confounding in this study, except by calendar time and possibly age, both of which are well recorded. Other possible sources of confounding we will be unable to address include clinical commissioning group, previous imprisonment and homelessness.

We anticipate that our estimate of PPI exposure times will be flawed to some extent due to lack of adherence. This will tend to lead to an underestimate of the effect size of any true association with lansoprazole, assuming the degree of exposure misclassification is non-differential in those people with and without subsequent TB disease.

As noted above, ethnicity will not be recorded for all patients and so the complete cases analysis including this variable may give a biased result. However, although ethnicity is a strong risk factor for TB, it is unlikely to be a strong deciding factor for specific PPI selection.

1. **Patient or user group involvement (if applicable)**

At this stage we do not plan to involve patients in the study; but depending on our findings it is possible we would seek patient engagement to help shape future research plans.

1. **Plans for disseminating and communicating study results, including the presence or absence of any restrictions on the extent and timing of publication**

All results will be presented at scientific conferences and published in a peer reviewed journal.

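### The Cox analysis names no allowance for clustering of patients within general practices, so its confidence intervals may be too narrow; the size cannot be fixed from the protocol and runs from negligible to material

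*Protocol*

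**What the plan says.** The Data/ Statistical analysis section of the protocol states: "Cox regression will be used to estimate hazard ratios and 95% confidence intervals, comparing lansoprazole exposed time against omeprazole or pantoprazole exposed time". It continues: "A crude model will be constructed with just the main exposure variable, followed by a model adjusting for potential confounders". General practice is not in the covariate list, and no variance estimator is named.

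Three other places bear on this:

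- Plan for addressing confounding: "local prescribing guidance for preferred PPI has varied over the years mainly based on cost considerations". This is offered mainly as the reason for treating calendar year as a confounder.
- Data Linkage Required: TB risk is expected to vary with socioeconomic status, and for patients outside the linkage scheme "we propose to use practice-level index of multiple deprivation for the remainder of patients". A practice identifier is therefore needed in any case.
- Limitations: ethnicity is called a strong TB risk factor, and the authors add: "Other possible sources of confounding we will be unable to address include clinical commissioning group, previous imprisonment and homelessness". Locality is thus treated as a possible source of bias and is not mentioned as a matter of precision.

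Table 1 in Sample Size is "based on a conservative 1:1 comparison between lansoprazole and omeprazole or pantoprazole" and mentions no design effect. The two rows that matter are "0.9 | 0.73 | 0.56 | 0.38 | 0.18" and "0.8 | >0.99 | >0.99 | 0.94 | 0.61", for 1,200, 800, 500 and 200 exposed cases.

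**The concern.** The cohort takes every eligible new user from the contributing practices, so patients come in clusters. A Cox model with its usual standard error takes patients as independent given the covariates. That does little harm if only the outcome, or only the exposure, varies between practices. When both do, events in a practice with high TB risk tend to fall in the same exposure group. The log hazard ratio then varies more from sample to sample than the model-based standard error allows. This is a fault in precision. It arises even if high-risk practices have no systematic preference for either drug, and so it is separate from confounding by locality.

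The protocol calls itself a hypothesis-testing study, and its first amendment reports a protective association that then prompted control analyses for MI and herpes zoster. If the intervals are too narrow, a chance imbalance between practices is more easily read as a drug effect. The control outcomes are read from intervals of the same kind. For a common outcome the events per practice, and hence the possible inflation, are larger.

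**Working it through.** **1. Table 1 contains no clustering allowance.** Two-sided alpha of 0.05 is assumed, in line with the 95% intervals. With c exposed cases, 2c events in total and a 1:1 split, power = Φ(√(2c × 0.25) × |ln RR| − 1.96). For RR 0.8 and c = 500: √250 × 0.2231 = 3.528, and Φ(1.568) = 0.942.

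| RR | 1,200 | 800 | 500 | 200 |
|---|---|---|---|---|
| 0.9, recomputed | 0.733 | 0.559 | 0.384 | 0.182 |
| 0.9, stated | 0.73 | 0.56 | 0.38 | 0.18 |
| 0.8, recomputed | 1.00 | 0.994 | 0.942 | 0.607 |
| 0.8, stated | >0.99 | >0.99 | 0.94 | 0.61 |

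Both rows are reproduced by the formula for independent patients. (One other cell, RR 0.7 with 200 cases, is stated as >0.99 where this formula gives 0.946. That is a separate matter from clustering.)

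**2. Size of the inflation.** None of the inputs in this step is in the protocol. I assume 650 or 400 practices, a coefficient of variation (CV) of practice size of 0.5, a CV of the residual practice TB hazard of 0.3 to 1.0, and a within-practice correlation of PPI choice of 0.1 to 0.3. Approximately,

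design effect = 1 + (events per practice × (1 + 0.5²)) × (hazard CV)² × (correlation of PPI choice).

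The false-positive rate of a nominal 5% test is then 2Φ(−1.96/√design effect). With 1,200 exposed cases and 650 practices there are 2,400/650 = 3.69 events per practice, and 3.69 × 1.25 = 4.62. For 500 exposed cases the factor is 1,000/650 × 1.25 = 1.92.

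| Hazard CV / correlation | 1,200 cases: design effect, false-positive rate | 500 cases: design effect, false-positive rate |
|---|---|---|
| 0.3 / 0.1 | 1.04, 5.5% | 1.02, 5.2% |
| 0.5 / 0.2 | 1.23, 7.7% | 1.10, 6.1% |
| 0.8 / 0.2 | 1.59, 12.0% | 1.25, 7.9% |
| 1.0 / 0.3 | 2.38, 20% | 1.58, 12% |

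With 400 practices and 1,200 cases the last three rows become about 10%, 16% and 28%. With 200 exposed cases and 650 practices the range is about 5% to 8%. Simulation under no drug effect gave rates within about one percentage point of these where it was run, and the practice-clustered sandwich test held 5% to 6% throughout.

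A second simulation used 650 practices, log-normal practice risk and no covariate adjustment. With no variation in PPI preference between practices, the design effect was about 1.0. With a log-SD of practice risk of 0.3 it was about 1.0 to 1.15, with coverage of the unadjusted 95% interval of 0.93 to 0.96. With moderate to strong preference variation it was 1.03 to 1.6 at log-SD 0.6 (coverage 0.87 to 0.95) and 1.2 to 3.5 at log-SD 1.0 (coverage 0.71 to 0.92).

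For a control outcome with an assumed 60 events per practice, hazard CV 0.2 and correlation 0.2, the design effect is 1 + 75 × 0.04 × 0.2 = 1.6, a false-positive rate of about 12%.

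**3. Effect on power at RR 0.8.** Replace 2c by 2c/design effect:

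| Design effect | 1,200 | 800 | 500 | 200 |
|---|---|---|---|---|
| 1.25 | 0.998 | 0.979 | 0.884 | 0.514 |
| 1.5 | 0.994 | 0.954 | 0.821 | 0.445 |
| 2.0 | 0.972 | 0.884 | 0.704 | 0.351 |

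**4. The 1:1 basis works the other way.** The feasibility counts are 744,144 and 1,182,888 new users, a ratio of 1:1.59. If comparator events follow that ratio (an assumption), the variance relative to 1:1 is (1 + 1/1.59)/2 = 0.81, which offsets a design effect of 1/0.8145 = 1.23. For 500 exposed cases at RR 0.8, power is 0.974 without clustering and 0.938 with a design effect of 1.25, against the stated 0.94.

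**The case against.** The strongest reply is that the protocol never says patients are treated as independent. That is inferred from a plain Cox model and silence, and a variance estimator is often left to a statistical analysis plan, which is not shown here. This stands against any statement that the intervals are wrong. It does not remove the point: the protocol sets out its models and sensitivity analyses in some detail, the first amendment says the study was run as outlined, and Table 1 demonstrably makes no allowance.

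The remark on local guidance mainly concerns change over time. If a practice's preference shifts over the years, the correlation of PPI choice pooled over follow-up falls. Adjustment for ethnicity, deprivation and calendar year would also lower the residual variation. Both points stand and push the effect down. They do not help the crude model, and ethnicity enters only through a complete-case analysis with substantial missing data.

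The larger error rates need about 1,200 exposed cases. The protocol's count of 1,227 is all TB after starting lansoprazole, during or after exposure, so 1,200 is near a ceiling. This also stands.

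A reader might infer that the reported hazard ratio is definitely overprecise, or that the protective association is an artefact of clustering. The documents support neither, since they give no practice count and no between-practice variation. A reader might also infer that the Table 1 powers are upper limits. Step 4 shows why that does not follow.

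**Conclusion.** The point holds as a possibility and is worth a cheap correction. The planned analysis names no allowance for practice clustering, although the protocol itself describes local influence on PPI choice and names TB risk factors that plausibly vary by locality. If PPI choice and residual TB risk both vary between practices, model-based intervals may be too narrow.

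Under the stated assumptions the effect is negligible with low variation, few exposed cases or effective adjustment. The design effect is about 1.2 to 1.6 or more with many exposed cases and strong variation, which widens a valid interval on the log scale by a factor of about √1.2 = 1.10 to √1.6 = 1.26.

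The conclusion of adequate power at RR 0.8 with 500 or more exposed cases largely stands. On the 1:1 basis power stays at or above 0.82 up to a design effect of 1.5, and falls to 0.70 only for 500 cases with a design effect of 2.0. The 200-case cell was already low at 0.61.

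**What to change.** Add to Data/ Statistical analysis: *All Cox models (TB, MI and herpes zoster; crude, adjusted and sensitivity analyses) will use robust (sandwich) standard errors clustered on general practice.*

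Beneath Table 1, add: *Powers assume independent patients and a 1:1 comparison; no design effect is applied.* Do not describe them as upper limits.

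The cost is one sentence, one note and one option in the model command. The practice identifier is already needed for practice-level deprivation. Point estimates do not change, and intervals may be somewhat wider.

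Two limits should be stated alongside. Clustering on practice does not remove confounding by locality or clinical commissioning group, which the protocol already concedes. Nor does it capture correlation above practice level, for example where several practices share one body of local guidance.

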CPRD linked Hospital Episodes Statistics (HES) in- and out-patient data will also be searched for codes indicating tuberculosis (A15-A19). A sensitivity analysis restricted to the CPRD HES-linked practices and time periods will be conducted, taking the earliest of CPRD or HES identified TB disease.

Covariates to be explored for their potential confounding nature will be age, sex, calendar year, smoking behaviour, body mass index, alcohol use, ethnicity, drug abuse, the use of inhaled/oral corticosteroids, travel vaccines, antimalarials, diabetes, rheumatoid arthritis, irritable bowel disease, chronic obstructive pulmonary disease, asthma, chronic kidney disease, depression, leukaemia, lymphoma, myeloma any record signifying the use of chemotherapy, a record of HIV infection and index of multiple deprivation score. Of note, ciclosporin and tacrolimus, both immunosuppressive drugs, are known to interact with omeprazole but not other PPIs. It is possible that people at higher risk of TB will therefore be given PPIs other than omeprazole and for this reason, patients with a history of use of either drug will be excluded from the study population.

1. **Data/ Statistical analysis**

Each participant’s follow up time will begin at the first prescription for lansoprazole or omeprazole/pantoprazole. All subsequent time will be classified as one of the following

- *Lansoprazole exposed* – all time covered by lansoprazole prescriptions, including a 60 day period after the estimated end of treatment date, to allow for stock piling and non-adherence
- *Omeprazole/pantoprazole exposed* – all time covered by omeprazole/pantoprazole prescriptions including a 60 day period after the estimated end of treatment date, to allow for stock piling and non-adherence. This will be the baseline against which other exposures are compared.
- *Unexposed* – all time between lansoprazole/omeprazole/pantoprazole exposure periods, or between the end of PPI exposure and the end of follow up. This time is being handled separately as it is plausible that a period of time off a PPI may be a marker of important changes in underlying health, with an associated change in the risk of TB disease

Where patients switch directly between one PPI and another, exposure will be updated to the new PPI from the date it is prescribed, assuming stock-piled drug is no longer taken.

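### The ethnicity-adjusted and HES analyses each change the patients along with the model or outcome, and no same-subset reference fit is named, so a shift in the hazard ratio could not be attributed

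*Protocol*

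**What the plan says.** **Ethnicity.** The protocol section Plan for addressing missing data expects under 10% missing for smoking, alcohol and BMI. It accepts complete-case analysis there because so little is missing. It then says ethnicity will have substantially more missing, gives no figure, and continues: "Again, we will conduct a complete case analysis with this variable included in the model, recognising the reduction in sample size will be greater". The Limitations section adds that "the complete cases analysis including this variable may give a biased result", and then argues that ethnicity, though a strong TB risk factor, is unlikely to decide which PPI is chosen.

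**HES.** The section Data Linkage Required gives the purpose: "We will also use HES (in- and out-patient data) to identify cases of TB recorded in hospital". The section Exposures, Outcomes and Covariates defines the analysis: "A sensitivity analysis restricted to the CPRD HES-linked practices and time periods will be conducted, taking the earliest of CPRD or HES identified TB disease". The primary outcome rests on the CPRD codes in Appendix 1. The application form (Section D, Data linkage) warns that linkage does not cover all CPRD patients and that coverage periods can differ between sources.

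**Models named.** The Data/Statistical analysis section names a crude Cox model and one adjusted for potential confounders. No fit without ethnicity is named for the patients who have ethnicity recorded. No CPRD-only outcome fit is named for the HES-linked practices and periods.

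**The concern.** Each analysis exists to answer one question: does adjusting for ethnicity change the result, and does wider case finding change it? As specified, each also changes who is analysed. A difference from the main hazard ratio then has at least two possible sources, and the planned outputs report only their sum. Absence of movement is not clear evidence either, because an adjustment effect and a selection effect in opposite directions could cancel.

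This matters because the first Amendment reports a protective association between lansoprazole and TB. If the ethnicity-adjusted hazard ratio lay closer to 1, a reader would need to know whether ethnicity explained part of the association, or whether patients with recorded ethnicity simply gave a different estimate.

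**Working it through.** **1. Ethnicity, split into its parts.** Write the log hazard ratios as:
- A: adjusted model without ethnicity, full cohort (complete on the other covariates)
- B: the same model, ethnicity-complete patients only
- C: model with ethnicity, ethnicity-complete patients only

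Then C − A = (C − B) + (B − A). C − B is the effect of adjusting for ethnicity. B − A is the effect of restricting the patients. The protocol names C, and A on the reading that the ethnicity model is additional to the main adjusted model. It does not name B, so one known difference has two unknown parts. If ethnicity is instead part of the only adjusted model, the crude-to-adjusted comparison mixes adjustment and restriction in the same way.

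**2. HES, split into its parts.** Write the log hazard ratios as:
- D: CPRD outcome, full cohort
- E: CPRD outcome, HES-linked practices and periods
- F: CPRD-or-HES outcome, the same linked subset

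Then F − D = (F − E) + (E − D). F − E is the effect of case finding. E − D is the effect of population and period. E is not named.

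**3. Does the complete-case argument carry over?** For smoking, alcohol and BMI it rests on the missing share being small. The protocol itself says the share is larger for ethnicity, so that reason lapses. The remaining argument, that ethnicity is unlikely to drive PPI choice, concerns confounding (C − B). It says nothing about restriction (B − A).

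**4. The plan's own power figures.** Inputs: "based on a conservative 1:1 comparison between lansoprazole and omeprazole or pantoprazole"; two-sided 5% assumed from "Cox regression will be used to estimate hazard ratios and 95% confidence intervals"; total events taken as 2 × exposed cases.

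Power = Φ(|ln RR| × √(events/4) − 1.96)

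At RR 0.8, |ln RR| = 0.2231. With 500 exposed cases: 0.2231 × √250 − 1.96 = 1.57, giving 0.942 (stated 0.94). The rest of that row gives 0.9998, 0.994 and 0.607 for 1,200, 800 and 200 cases (stated >0.99, >0.99, 0.61). The formula reproduces 19 of the 20 cells of Table 1. The exception, RR 0.7 with 200 cases (0.946 against >0.99), is not used here.

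**5. How large can B − A be by chance alone?** On the same basis, the variance of a log hazard ratio is about 4/events. If events are lost at random, the variance of B − A is about 4/(events kept) − 4/(all events). The missing share is an assumption, because the protocol gives none.

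With 500 exposed cases and 50% missing: 4/500 − 4/1,000 = 0.004; √0.004 = 0.0632; exp(1.96 × 0.0632) = 1.13. A full-cohort hazard ratio of 0.80 could then appear anywhere from 0.80/1.13 = 0.71 to 0.80 × 1.13 = 0.91.

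| Exposed cases | Assumed missing | 95% factor for B against A |
|---|---|---|
| 500 | 10% | 1.04 |
| 500 | 30% | 1.08 |
| 500 | 50% | 1.13 |
| 500 | 70% | 1.21 |
| 1,200 | 50% | 1.08 |
| 800 | 50% | 1.10 |
| 200 | 50% | 1.22 |

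Systematic selection would add to this. The comparison C − B uses the same patients and events, so it carries none of this component.

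**The case against.** **The SAP is not shown, and such fits are often specified there.** This is fair as a caution: if a SAP names them, the point is closed. But the protocol does more than stay silent. It fixes the population, the model and the outcome of both analyses, and in that form the changes are mixed.

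**The ethnicity-complete patients are a nested subset, and the missing fits can be run at any time.** Both are true. A reader might infer that a shift could never be explained; the documents do not support that. Nothing prevents the extra fits, and the claim is only that the outputs now planned do not contain them.

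**Restriction to linked practices is unavoidable for HES.** This stands, and an analysis of robustness under restriction and wider case finding together is legitimate. It is also the reason to fit the CPRD-only outcome in the same subset.

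**Ethnicity is not expected to confound.** The protocol says so, and expects confounding mainly from calendar time and possibly age. It also plans time-shift, exposure-window and control-outcome analyses. A reader might therefore overstate the ethnicity model as the main check on the TB result; the documents do not give it that role.

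**Power.** A reader might infer that the ethnicity model is underpowered. The documents do not settle this. The protocol already concedes the smaller sample, gives no missing share, and says: "At this stage we cannot be sure how many incident TB cases will occur during PPI exposure, rather than after exposure has ended". At RR 0.8 with an assumed 50% missing, the formula gives 0.97, 0.88, 0.70 and 0.35 for 1,200, 800, 500 and 200 exposed cases, so the answer depends on two unknowns.

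**Filling the gaps.** A reader might suppose that the linked HES records could supply missing ethnicity. The protocol uses HES to find TB cases and nowhere says that HES holds ethnicity, so no finding is made on that.

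**Conclusion.** The point holds as one of attribution. Both analyses, as written, change the patients together with the feature under test, and the reference fit that would separate the two is not named in either. The protocol acknowledges possible bias in the ethnicity result without a means of seeing it, and its small-missingness argument does not extend to that variable.

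The direction and size of any actual shift cannot be determined from the documents. The chance component alone would be a factor of about 1.04 to 1.21 at 500 exposed cases, assuming 10% to 70% of events are lost at random, equal event numbers in the two exposure groups and the large-sample variance above. For HES, restriction removes cases while the hospital codes add some, so the net effect on precision cannot be determined either.

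This is a worthwhile, inexpensive improvement. It does not show that the reported TB association is wrong.

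**What to change.** 1. **Ethnicity.** Refit the adjusted model without ethnicity in exactly the patients used for the ethnicity model. Read the effect of ethnicity adjustment from that pair. Compare the without-ethnicity fit with the full-cohort fit to show the effect of selection. Report the share of patients, and of TB cases, with ethnicity missing.
2. **HES.** Fit the CPRD-only TB outcome in the same linked practices and periods, and compare the CPRD-or-HES outcome with that. Compare the CPRD-only fit with the full-cohort result to show the effect of restriction.

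The cost is two extra model fits on data already requested, with no new patients or linkage. Because the first Amendment states that the TB analysis has been run, fits added now should be labelled as specified after the main result was known.
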